### 6.2.2 Participants taking ACEI or ARB before inclusion

The Telmisartan arm is not assessed in this stratum. The 3 other arms only will be compared. We specify no sample size a priori. The proportion of persons taking ACEI or ARB is assumed to be 20% of the target population. Consequently, we expect to recruit 53 participants per arm (212 in total).

Following futility or efficacy analyses, the DSMB may recommend to increase the size to reach a sufficient power for clinically relevant statistical tests.

### 6.2.3 Overall sample size

Summing the sizes of both strata, and if all the arms go to the end of the trial, we get a final and overall size of 1057 participants. It is likely that one or more arms will be discontinued for futility and the number of participants will not reach this amount.

## 6.3 Analysis plan

A separate detailed statistical analysis plan will be written and validated by the SAB. Possible future modifications will lead to amendments written and validated before database freezing.

### 6.3.1 General information on the statistical techniques used

Qualitative outcomes will be described in tables and graphs as follows: frequency, proportion, standard deviation of the proportion, two-sided 95% confidence interval. Comparisons between arms will use a Chi test or an exact Fisher's test (depending on the outcome distribution) if no adjustment is required or logistic or binomial regression otherwise.

Normality of quantitative outcomes will be checked graphically.

Normally distributed quantitative outcomes will be described in tables and graphs as follows: frequency, mean, standard deviation of the mean, two-sided 95% confidence interval. Comparisons between arms will use a Student's t test if no adjustment is required or a linear model otherwise.

Quantitative non-parametric outcomes will be described in tables and graphs as follows: frequency, median, range and interquartile range. Comparisons between arms will use a Wilcoxon or a Kruskal-Wallis test (depending on the number of strata) if no adjustment is required or a stratified analysis otherwise.

Time-to-event outcomes will be described in tables and graphs as follows: number, probability of event and two-sided 95% confidence interval estimated by the Kaplan-Meier method. Comparisons between arms will use a logrank test if no adjustment is required or a proportional risk (Cox) model otherwise.

Model assumptions will be checked before final adjustment.

Descriptive analyses will be systematically presented globally, by country, stratum and arm.

Comparisons between arms will be systematically performed:

- Without adjustment
- With adjustment on randomisation stratification factors
- With adjustment on randomisation stratification factors and on baseline prognostic factors which distribution could be unbalanced between arms despite randomisation.

Moreover, these adjustments will possibly imply the use of appropriate models not cited here. Their relevance will be discussed depending on the factors nature and distribution.

Details on secondary and exploratory analyses on the primary endpoint and analyses on secondary and exploratory endpoints will be provided in the statistical analysis plan.

The identification of determinants of events will be performed using univariate and stepwise multivariate selection models, which details will be defined in the statistical analysis plan.

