### 1.4.1 Choice of study model

Preclinical and clinical data suggesting the effectiveness of drugs against SARS-CoV-2 are still limited. A trial launched in a context of emergency should be able to integrate those considered suitable under current knowledge, while allowing them to be discarded quickly, if they do not prove immediately promising. Drugs should be able to be included during the course of the trials if new promising evidence arise in the interim.

A multi-arm, multi-stage (MAMS) study would be more efficacious in this context than separated trials with two arms (experimental treatment vs. control). This type of trial, offering the opportunity to plan in advance to change one or several aspects of the trial, is particularly suited to the current, highly-evolving, scientific context. MAMS trials allow simultaneous comparison of a certain number of experimental treatments with a single control treatment. This type of

trial provides answers more rapidly and allows the abandonment of arms for futility over planned intermediate analyses or new scientific facts or even to add an arm over the course of the trial.

Three intermediate analyses are planned over the course of the trial, after recruiting 30, 60 and 102 participants per arm. They shall cause the halting of arms, should they prove futile or toxic. At the 3rd intermediate analysis, a preliminary efficacy analysis will allow identification of any treatment, which proves to be efficacious before the end of the trial. This treatment shall then become the standard. A halt on grounds of insufficient safety shall be possible at any point, subject to approval from the DSMB, without the need for a formal statistical criterion.

Multiple statistical tests shall be conducted on grounds of the multi-stage design and the existence of several arms. Type one alpha error shall not be adjusted on grounds of the absence of an objective to extend the indication. The objective is to identify all efficacious drugs and not to identify the best.

Overall, this type of model provides us with a concomitant optimisation of the evaluation of various therapeutic strategies, while adapting itself to the international scientific context and progressively evaluating the most promising strategy or strategies.

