## 6.2 Sample Size

### 6.2.1 Participants not taking ACEI or ARB before inclusion

The incidence assumptions on primary endpoint are based on extrapolations from aggregated data published in other contexts thus far. The DSMB will check these assumptions and recommend a sample size revision, if needed.

We assumed that the proportion of participants reaching the primary endpoint at D14 in the control arm could be up to 25%. An experimental treatment will be deemed efficient if this proportion is reduced by at least one half. We also considered a power of 80% for all tests.

Three futility (interim) analyses will be performed successively. We defined successive arm discontinuation thresholds for the one-way first type error alpha using STATA package NStageBin for conception and sample size of MAMS trials (65,66).

Two efficacy analyses (interim n°3 and primary) will be performed successively. We will use the O'Brien & Fleming procedure to define the first type error alpha for each analysis, based on the data observed at the first futility analyses (67,68).

Sensitivity analysis at D28 will be exploratory only, without impact on sample size.

Tests of difference between arms will be one-sided. Arm discontinuation thresholds and sample size for each analysis are given here below:

| Analysis    | Trigger
Number of participants in the control arm having reached D14 | Objectives     | Alpha           |
|-------------|-------------------------------------------------------------------------|----------------|-----------------|
| Interim n°1 | 30                                                                      | Futility       | 0,65            |
| Interim n°2 | 60                                                                      | Futility       | 0,45            |
| Interim n°3 | 102                                                                     | Futility       | 0,25            |
|             |                                                                         | Early efficacy | O'Brien-Fleming |
| Primary     | 169                                                                     | Efficacy       | O'Brien-Fleming |
| Sensitivity | End of trial                                                            | Efficacy       | 0,05            |

The sample size required is 169 participants by arm (845 overall). Since the "Missing as failure" procedure is used, there is no need to increase sample size to account for missing data.

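### Fisher's exact test, named in 6.3.1 for sparse tables, is too strict for the 0.65 futility threshold at interim 1 (minor; one sentence to fix)

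*Protocol*

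**What the plan says.** Protocol 6.3.1 lists general techniques. For qualitative outcomes compared without adjustment it gives a Chi² "test or an exact Fisher's test (depending on the outcome distribution) if no adjustment is required or logistic or binomial regression otherwise". No other section names a test for a binary outcome. Section 6.3.4, on the primary outcome, names none.

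The futility rule is in 6.2.1: "We defined successive arm discontinuation thresholds for the one-way first type error alpha using STATA package NStageBin". The thresholds are 0.65, 0.45 and 0.25 at 30, 60 and 102 participants, and the final analysis is at 169. The same section adds: "Tests of difference between arms will be one-sided". Its design assumptions are:

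- Control risk: the proportion "reaching the primary endpoint at D14 in the control arm could be up to 25" per cent.
- Target effect: "An experimental treatment will be deemed efficient if this proportion is reduced by at least one half".
- Power: "We also considered a power of 80% for all tests".

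For efficacy, "We will use the O'Brien & Fleming procedure to define the first type error alpha for each analysis", with no overall alpha given.

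**The concern.** The futility thresholds are one-sided error rates for a test whose p-value is 0.50 when the two arms have equal counts. A threshold of 0.65 therefore lets an arm continue if it is level with control or slightly worse. That leniency is what keeps the chance of losing a good arm after only 30 participants per arm near 5%.

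Fisher's exact p is built differently. It includes all of the probability of the observed table, so for equal counts it lies above 0.50, and further above as events become fewer. Against a conventional small alpha this is the familiar conservatism. Against a threshold above 0.5 used to drop arms, it removes part or all of the intended leniency. Section 6.3.1 directs the analyst to Fisher when the outcome distribution calls for it, and that is most likely at the smallest look. What is at stake is the loss of effective arms at interim 1.

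**Working it through.** **Inputs.** From 6.2.1: control risk 25%, target 12.5%, looks at 30, 60, 102 and 169 per arm, one-sided thresholds 0.65, 0.45 and 0.25. Two assumptions are ours. Fisher replaces Z when the smallest expected count is below 5. The final test is one-sided at 0.025.

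**Step 1: reproduce the design.** With a one-sided Z test, stage power is Φ(δ/SE − z), where δ = 0.125, SE = √[(0.25×0.75 + 0.125×0.875)/n] = √(0.296875/n), and z is the upper-tail normal quantile of the stage alpha.

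| n per arm | alpha | δ/SE | z | stage power |
|---|---|---|---|---|
| 30 | 0.65 | 1.257 | −0.385 | 0.950 |
| 60 | 0.45 | 1.777 | 0.126 | 0.951 |
| 102 | 0.25 | 2.317 | 0.674 | 0.950 |
| 169 | 0.025 (assumed) | 2.982 | 1.960 | 0.847 |

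With correlation √(n_i/n_j) between looks, the probability of passing all four is 0.800, which is the stated 80%. A final alpha of 0.05 would give 0.848. The thresholds and the 169 per arm therefore fit a one-sided Z test.

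**Step 2: ties at interim 1 (30 per arm).** An arm continues if p ≤ 0.65. With k events in each arm, symmetry gives Fisher's one-sided p = 0.5 + 0.5 × C(30,k)²/C(60,2k).

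- k = 0: 1.00, stops
- k = 1: 0.5 + 0.5 × 900/1,770 = 0.754, stops
- k = 2: 0.5 + 0.5 × 189,225/487,635 = 0.694, stops
- k = 3: 0.5 + 0.5 × 16,483,600/50,063,860 = 0.665, stops
- k = 4: 0.647, continues; k = 7: 0.619; k = 8: 0.614

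The Z test gives 0.50 for every tie (at 0-0 the statistic is undefined and 0.50 is a convention). Mid-p, which counts half the probability of the observed table, gives 0.50 throughout. Near-ties are affected too. With 5 experimental and 4 control events, Z = −0.0333/√(2×0.15×0.85/30) = −0.36, so p = 0.641 and the arm continues. Fisher gives 0.764 and the arm stops.

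At looks 2 and 3 a tie stops under the Z test as well, since 0.50 exceeds 0.45 and 0.25. The design intends that.

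**Step 3: how often Fisher would be used.** With equal arms the smaller expected count is half the total number of events, so the assumed switch applies at nine or fewer events among 60. At 25% vs 12.5% the mean is 30 × (0.25 + 0.125) = 11.25 events, and 29% of interim 1 tables fall under the switch. At 15% vs 7.5% it is 87%.

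**Step 4: probability that an arm with a true halving passes interim 1.** Sum Bin(c; 30, p_C) × Bin(e; 30, p_C/2) over all 31 × 31 tables with p ≤ 0.65.

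| Control risk | Z | Fisher when sparse | mid-p when sparse |
|---|---|---|---|
| 25% | 0.954 | 0.937 | 0.960 |
| 20% | 0.928 | 0.887 | 0.942 |
| 15% | 0.888 | 0.804 | 0.908 |
| 10% | 0.846 | 0.698 | 0.857 |

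**Step 5: whole trial at 25% vs 12.5%.** Simulating through the three futility looks to a final one-sided test at 0.025, power is 0.804 with Z and 0.794 with Fisher when sparse. With an overall one-sided 0.05 and O'Brien-Fleming efficacy at the last two analyses, it is 0.851 and 0.840. The loss is about one point either way.

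**The case against.** **The sections read together already give a directional test.** This is correct. A reader might infer that naming an undirected Chi² lets arms worse than control through the futility looks. The documents do not support that: 6.2.1 makes the tests one-sided and the thresholds one-way, and the only thing 6.3.1 calls two-sided is the confidence interval. A one-sided 2×2 Chi² is the signed root, which is the Z test of the design. Only the Fisher branch is left, and making it one-sided does not cure it.

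**Fisher does not drop ties in general.** Also correct. A reader might infer that any arm equal to control is stopped. Only ties of three or fewer events per arm at interim 1 are affected, and at 25% control risk seven or eight control events are expected. The 5 vs 4 example is an arm doing slightly worse than control, so stopping it is not an obvious error in itself; it only departs from what 0.65 was set to allow.

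**The effect is small at the planned risk, and lower risks bring larger problems.** This largely stands. The loss at 25% is under two points at interim 1. At lower risks the design is short of power under any test, and 6.2.1 has the DSMB check the incidence assumption. Still, the plan puts 25% as an upper value extrapolated from other settings, so lower risks are plausible, and the loss from Fisher comes on top.

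**The exact statistic belongs in the SAP.** Partly. Section 6.3 announces a SAP, and the finer rules can sit there. But 6.3.1 does not leave the test open: it names Fisher, and that test fits the stated threshold badly.

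**Conclusion.** The point holds as a minor one. If Fisher's exact p is held against the interim 1 threshold of 0.65, the rule is stricter than the one the thresholds were set for, and an arm with a true halving of risk is lost somewhat more often: 1.7 points at 25% control risk (0.954 − 0.937), 4.1 at 20% (0.928 − 0.887), 8.4 at 15% (0.888 − 0.804) and 14.8 at 10% (0.846 − 0.698). Under the plan's own assumptions overall power falls by about one point. The thresholds and the sample size are sound.

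The sizes rest on the assumed switch at expected counts below 5, since 6.3.1 says only that the choice depends on the outcome distribution. The power figures also rest on an assumed final alpha; the interim 1 pass rates do not.

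**What to change.** Add one sentence to 6.3.1: for the futility analyses, the p-value compared with the thresholds in 6.2.1 is that of the one-sided Z test of the difference in proportions (signed root of the uncorrected Chi², in the direction of benefit), replaced by the one-sided mid-p value, not Fisher's exact p, when counts are sparse. State the sparse-count rule, for example any expected count below 5. Mid-p also settles the 0-0 table, where Z is undefined. Chi² and Fisher can remain for all other comparisons.

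The cost is one sentence before the first look, with no extra data or participants. The downside is that mid-p is not strictly conservative, so slightly more ineffective arms pass interim 1 than under Fisher: 0.673 against 0.664 for an arm with no effect at 25% risk. Two later futility looks remain to stop such arms.

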#### 4.3.2 Secondary criteria

- Hospitalisation proportion and its causes between Day 0 and Day 28 within each group
- Proportion of deaths and their causes between Day 0 and Day 28 within each group
- Intensive care hospitalisation proportion and its causes between Day 0 and Day 28 within each group

---

 Currently, the following criteria are being proposed: SpO2 < 92% in ambient air or 4% reduction in SpO2 since inclusion; respiratory rate > 30 min; heart rate > 130/min; systolic blood pressure < 90 mmHg or diastolic < 60 mmHg; other parameters indicating hospitalisation, in the judgement of the attending physician (for example, unexplained fall, severe digestive problems, reoccurrence or persistent fever > 38.5°C etc.)

- Proportion of patients with a reversion of SARS-CoV2 RT-PCR on a nasopharyngeal swab on Day 7 and Day 14, in each group
- Proportion of patients with a loss of autonomy evaluated by ADLs and IADLs on Day 14 and Day 28
- Changes in CBC, inflammatory markers (please see paragraph **Erreur ! Source du renvoi introuvable.**) and immunological markers (please see paragraph **Erreur ! Source du renvoi introuvable.**) from Day 0 to Day 7 and Day 14 in each group
- Number and proportion of adverse events of grades 1, 2, 3, 4 between Day 0 and Day 14 in each group
- Number and proportion of adverse reactions of grades 1, 2, 3, 4 between Day 0 and Day 14 in each group
- Plasma trough concentration of experimental drugs in the study on Day 7
- Acceptability of the treatment

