#### 5.3.10.2 Blood tests

Blood samples are to be taken on Day 0, Day 7 and Day 14 transported and processed in the laboratory according to a standard procedure [SDPM].

Blood samples are to be used thus:

- The day of sampling (on Day 0, Day 7 and Day 14): CBC, PCT, CRP, ferritin, creatinine, urea, sodium, potassium, chloride, calcium, magnesium, albumin, bicarbonates/tCO2, LDH, CPK, ASAT, ALAT on Day 0, Day 7 and Day 14.
- Remotely, on frozen plasma and kept in biobanks:
  - On Day 7 for later pharmacological examination (measurement of plasma trough concentrations of the drugs by HPLC/MS-MS)
  - On Day 0, Day 7 and Day 14 for immunological examination, if the patient has agreed to participate in the immunological sub-study [SDPM] (please see paragraph **Erreur ! Source du renvoi introuvable.**)

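### Section 6.3.1 does not assure adjustment of the blood-count and inflammatory-marker comparisons for the marker's own Day 0 value, which is already collected

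*Protocol*

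**What the plan says.** Section 4.3.2 lists a secondary criterion that opens "Changes in CBC, inflammatory markers (please see paragraph" and covers the interval "from Day 0 to Day 7 and Day 14 in each group". Section 5.3.10.2 provides the matching measurements: "The day of sampling (on Day 0, Day 7 and Day 14): CBC, PCT, CRP, ferritin", among other tests.

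Section 6.3.1 sets general methods for all quantitative outcomes and names no marker. If an outcome looks normal on a graphical check, "Comparisons between arms will use a Student's t test if no adjustment is required or a linear model otherwise". If it does not, "Comparisons between arms will use a Wilcoxon or a Kruskal-Wallis test (depending on the number of strata) if no adjustment is required", with a stratified analysis when adjustment is wanted. The section then makes three comparisons systematic. The first has no adjustment, and the second adjusts for the stratification factors. The third is described as "With adjustment on randomisation stratification factors and on baseline prognostic factors which distribution could be unbalanced between arms despite randomisation". Section 4.4 names place of residence as the stratification factor, with separate lists by prior use of renin-angiotensin blockers. Section 6.3.1 also says that details of "analyses on secondary and exploratory endpoints will be provided in the statistical analysis plan".

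**The concern.** The covariate rule in 6.3.1 selects baseline factors by possible imbalance between arms. For most baseline characteristics that is a familiar, if weak, convention. For the Day 0 measurement of the outcome itself it misses the purpose. That value removes variance in proportion to its correlation with the follow-up value, whether or not the arms differ at Day 0. A rule triggered by imbalance also lets the observed data decide which model is fitted.

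An SAP could follow 6.3.1 to the letter and never include the Day 0 value. Arm differences in CRP, ferritin, procalcitonin and blood counts would then be estimated less precisely than the collected data allow. Precision may already be stretched. Section 5.3.9 lets Day 7 and Day 14 visits become remote with their samples dropped, and 6.3.6 analyses secondary endpoints on available data.

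**Working it through.** **Plan's own figure.** The protocol states no standard deviation, target difference, correlation or power for any marker, so there is none to reproduce. The 169 per arm in 6.2.1 belongs to the binary primary endpoint. It is used below only as a scale.

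**What each comparison contains.**

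| Comparison in 6.3.1 | Marker's Day 0 value as covariate? |
|---|---|
| Unadjusted | No |
| Adjusted for stratification factors | No |
| Adjusted for strata and possibly unbalanced baseline factors | Only if judged to meet the imbalance criterion |

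**Formulas.** Let s0 and s1 be the standard deviations at Day 0 and follow-up, and rho their correlation within arm.

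- Variance of the change: s0² + s1² − 2·rho·s0·s1
- Residual variance after adjusting for Day 0: s1²(1 − rho²)
- Difference between the two: (s0 − rho·s1)², which is never negative

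Apart from the degree of freedom spent on the covariate, adjustment therefore does not lose precision against the change score. With s0 = s1, in units of the marker variance, the two variances are 2(1 − rho) and 1 − rho². Their ratio is (1 + rho)/2.

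**Power.** Take a difference that a t test on change detects with 80% power at two-sided 5%, so that the expected z value is 1.96 + 0.84 = 2.80. After adjustment, power = P(Z > 1.96 − 2.80/√ratio).

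| Assumed rho | Variance of change | Adjusted variance | Ratio | Fall in standard error | Power (from 80%) | Adjusted n per arm giving the precision of 169 on change |
|---|---|---|---|---|---|---|
| 0.3 | 1.40 | 0.91 | 0.65 | 19.4% | 94% | 110 |
| 0.5 | 1.00 | 0.75 | 0.75 | 13.4% | 90% | 127 |
| 0.7 | 0.60 | 0.51 | 0.85 | 7.8% | 86% | 144 |
| 0.9 | 0.20 | 0.19 | 0.95 | 2.5% | 82% | 161 |

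The last column is 169 × ratio, rounded up. At rho 0.5, for example, 2.80/√0.75 = 3.23, 3.23 − 1.96 = 1.27, and the power is 0.90.

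**Limit of the check.** The figures compare a t test on change with a linear model. They do not carry over to the rank-test route for non-normal markers. The stratified analysis offered there has no natural place for a continuous Day 0 value.

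**The case against.** The strongest reply is that 6.3.1 leaves the details of secondary-endpoint analyses to an SAP that is not at hand. A covariate list for a laboratory endpoint is ordinary SAP content, and its absence from a protocol would be no finding. That stands as far as silence goes. But 6.3.1 is not silent. It states how baseline factors qualify, and an SAP that follows it need not include Day 0.

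Three stronger readings are tempting, and the protocol does not support them:

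- **That no adjustment for Day 0 is planned.** The sentence on the t test itself offers a linear model, adjusted comparisons are systematic, and the third can admit the Day 0 value. The section also leaves room for models it does not name. Nothing excludes Day 0; it is simply not assured.
- **That every marker goes to a t test on change.** The t test applies only to outcomes judged normal. Applying it to the marker changes comes from joining 4.3.2 to general text.
- **That regression to the mean biases the comparison.** In randomised arms it acts alike in expectation. It matters only through a chance Day 0 difference in the trial at hand, which the third comparison may address.

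The size is also assumed. Rho is unknown, equal standard deviations may not hold in acute illness, no marker comparison was powered at 80%, and the gain nearly vanishes at high rho.

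**Conclusion.** The point holds as a minor improvement. The imbalance rule is a stated and inferior basis for choosing the covariate that matters most for these endpoints, and the better choice uses data already planned. Under equal standard deviations the variance falls by 35% at rho 0.3, 25% at 0.5, 15% at 0.7 and 5% at 0.9. The power gain runs from about 14 points down to about 2. All of this rests on an assumed rho, because the protocol supplies none.

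The planned unadjusted comparison is valid but less precise. The primary endpoint, the sample size and the stopping thresholds are unaffected.

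**What to change.** In 6.3.1, and then in the SAP, state that for each marker at Day 7 and at Day 14 the arms are compared by a linear model of the follow-up value, on the log scale where the marker is skewed. The model contains arm, that marker's Day 0 value and the randomisation strata, whatever imbalance is observed. Keep the change from Day 0 as a description, in line with 6.3.3.

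The cost is one sentence of analysis text, with no new samples, visits or participants. Those without a Day 0 sample are already lost to a change score. Section 6.3 says the SAP is still to be written, so the wording can go in from the start.

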### 3.2 Secondary objectives

The study's secondary objectives are:

- Appraise the efficacy of several experimental treatments of SARS-CoV-2 infection, compared with standard of care, to prevent death on Day 28
- Appraise the efficacy of several experimental treatments of SARS-CoV-2 infection, compared with standard of care, to prevent hospitalisation on Day 28
- Appraise the efficacy of several experimental treatments of SARS-CoV-2 infection, compared with standard of care, to prevent admission to intensive care unit on Day 28
- Appraise the efficacy of several experimental treatments of SARS-CoV-2 infection to eliminate nasopharyngeal carriage of the virus, compared with standard of care
- Appraise the efficacy of several experimental treatments of SARS-CoV-2 infection, compared with standard of care, to prevent loss of autonomy
- Appraise tolerance of experimental treatments against SARS-CoV-2 infection
- Study those factors associated with clinical deterioration in patients with COVID-19
- Evaluate the feasibility and acceptability of the trial and model of care model implemented.
- Evaluate the relationship between concentrations for each drug and efficacy of each of the treatments

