### 9.1.4 Scale of the study

The number of people participating in this study is to depend on the take-up rate.

In total, 30 patients/arms with all measures (maybe 150 in total). This scale of sampling allows description of the phenotypic and functional profile of each arm upon inclusion and evolution over time with enough precision (72,73).

In the event of good take-up, the study of the genetic expression profile on cotton swabs could be proposed for all patients included in the main study. 20 to 40 events per treatment group are expected, which would make 100 to 200 events in total at the end of the trial, if all the participants in the main trial agree to participate in this sub-study; possibly 10 to 20 clinical progression predictors are possible with the conservative rule of 10 events per predictor (74).

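### Protocol 6.3.1 fixes stepwise selection for the factors associated with deterioration; a single prespecified model would be less biased and costs almost nothing

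*Protocol*

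**What the plan says.** Section 6.3.1 of the protocol says that the determinants of events will be identified with "univariate and stepwise multivariate selection models". It adds "which details will be defined in the statistical analysis plan". The family of methods is therefore fixed in the protocol; thresholds and the list of candidates are not.

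The objective that this most plainly serves is in section 3.2: "Study those factors associated with clinical deterioration in patients with COVID-19". Section 11.2 (Impact) also counts data on the risk of worsening and its associated factors among the trial's expected contributions. The link between determinants of events and this objective is an inference, but no other listed objective fits as well.

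The immunological sub-study has provisions of its own. Section 9.1.4 expects 20 to 40 events per group and 100 to 200 in total if all main-trial participants take part, and concludes that "10 to 20 clinical progression predictors are possible with the conservative rule of 10 events per predictor". Section 9.1.5 provides False Discovery Rate control for changes from baseline. Neither is stated for the analysis in section 6.3.1.

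**The concern.** Stepwise selection keeps the variables whose estimates happen to be large in the sample at hand. If the retained model is then reported as though it had been chosen in advance, two things follow. The coefficients of retained variables are on average too far from zero. The printed confidence intervals take no account of the choice, so they cover the truth less often than they claim. The retained set can also change with small changes in the data when candidates are correlated, as several of the Day 0 laboratory items in section 5.3.10.2 plausibly are.

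At stake is the list of risk factors for worsening that the trial intends to publish, and the strength given to each. No treatment comparison depends on it.

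**Working it through.** **1. Events available.** Inputs from section 6.2.1: 169 participants per arm, five arms, control rate up to 25%, and an effect defined as a halving, that is 12.5%.

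- Per arm: 169 × 0.125 = 21.1 and 169 × 0.25 = 42.3. Section 9.1.4 gives 20 to 40.
- Five arms: 5 × 21.125 = 105.6 and 5 × 42.25 = 211.3. Section 9.1.4 gives 100 to 200, the same figures in round numbers.
- Ten events per predictor: 100/10 = 10 and 200/10 = 20, as section 9.1.4 says.
- If control is 25% and all four experimental arms are 12.5%: 42.25 + 4 × 21.125 = 126.75 events, and 126.75/845 = 15%. If no arm works, the rate is 25%. These two rates were used below.

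**2. Assumed settings.** The protocol gives no number of candidates K, no thresholds and no effects. A simulation of logistic regression was therefore run over a range:

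- n = 845; event rate 15% or 25%; K = 10, 20 or 30; 300 runs per setting.
- Five candidates with a true log odds ratio of 0.2 per SD, the rest with no effect; correlation between candidates 0 or 0.3.
- Univariate entry at p<0.20, then backward elimination at p<0.05. The univariate entry step is itself an assumption.

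The comparison is the full model with all K candidates, fitted to the same data.

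**3. Results.** Ranges are over the two event rates and, where not split, the two correlations. Coverage is of nominal 95% intervals.

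| K | All retained variables | Retained true, correlation 0 | Retained true, correlation 0.3 | Full model, all coefficients |
|---|---|---|---|---|
| 10 | 80–89% | 94.4–96.2% | 89.6–91.4% | 94.4–95.0% |
| 20 | 70–78% | 94.4–96.6% | 90.7–92.0% | 94.6–94.9% |
| 30 | 60–70% | 95.5–96.9% | 89.5–91.4% | 94.0–94.6% |

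Mean ratio of estimated to true log odds ratio among retained true predictors:

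| K | Correlation 0 | Correlation 0.3 |
|---|---|---|
| 10 | 1.21–1.37 | 1.39–1.55 |
| 20 | 1.21–1.37 | 1.38–1.53 |
| 30 | 1.21–1.36 | 1.39–1.53 |

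In odds-ratio terms, a true value of exp(0.2) = 1.22 per SD would be reported at about exp(0.2 × 1.21) = 1.27 to exp(0.2 × 1.55) = 1.36.

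**4. Where the coverage is lost.** A null variable retained at p<0.05 has an interval that excludes its true value of zero, so it counts as a miss. Take K = 20, rate 25%, correlation 0. True predictors retained per model: 5 × 0.705 = 3.53. False ones: 0.83. Coverage of true ones: 0.966. Then 3.53 × 0.966 / (3.53 + 0.83) = 0.78, which matches the simulated 78%. Most of the loss in the first column comes from falsely retained variables. With correlated candidates, true predictors add a smaller loss.

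**The case against.** The strongest reply is that the harm is assumed rather than shown. Candidates, thresholds and any validation are left to a statistical analysis plan that is not at hand, and the aim is to study associated factors, not to deliver a validated prediction model. The first part stands: the figures above illustrate a range and do not predict this trial's result. The lack of a candidate list or a bootstrap in the protocol is also no fault in itself. What the reply does not remove is that the protocol names the selection method, so an analysis plan that follows it can tune stepwise selection but not replace it.

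Three stronger readings are tempting and are not supported.

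- **A false-positive figure as the argument.** A reader might compute 1 − 0.95^20 = 0.64 for at least one false determinant among 20 independent null candidates. That is multiplicity. A prespecified model with 20 null coefficients read at p<0.05 carries the same 64%, so it is no reason to prefer one method to the other.
- **A breach of the events-per-predictor rule.** The rule in section 9.1.4 belongs to the immunological sub-study. It is not applied to section 6.3.1, and nothing says how many candidates will be examined there. No breach is shown.
- **Univariate screening as stated policy.** The text names univariate and stepwise models but does not say that a univariate p-value decides entry. Showing univariate and multivariable results side by side fits the wording equally well.

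It is also fair to object that intervals for true, independent predictors held up, at 94% to 97%. That stands and limits the claim about intervals.

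**Conclusion.** The point holds as a low-severity, cheap improvement. The protocol fixes an inferior method for a secondary, exploratory objective.

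Under the assumed settings, retained true effects were inflated about 1.2 to 1.55 times, and intervals of retained variables covered the truth in about 60% to 89% against 94% to 95% for the full model. The coverage gap widens with the number of candidates. The inflation hardly depends on that number; it is larger with fewer events and with correlated candidates.

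Two limits apply. The full-model coverage refers to all coefficients; picking out only the significant ones would bring selection back. The simulation recorded coverage for the full model but not the bias of its coefficients. It also used the 845 participants of the main list with all arms continuing, whereas section 6.2.3 regards the loss of one or more arms as likely, which would mean fewer participants and usually fewer events.

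The primary comparison, its alpha and the sample size are untouched.

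**What to change.** In section 6.3.1, replace the stepwise selection models with one prespecified multivariable model, full or penalised, and carry this into the statistical analysis plan before the database is frozen:

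- Fix the candidates in advance and limit their number by the expected events, 100 to 200 if all arms continue and fewer if arms stop.
- Include randomised arm and randomisation list. The list term matters once both lists are analysed together, because telmisartan is allocated in only one of them.
- Report every coefficient, not only the significant ones, together with bootstrap-corrected performance.
- Show univariate results descriptively if wanted, but do not let them decide entry.
- Label the analysis hypothesis-generating.

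The cost is a change of wording and a little programming. The downside is a less sparse model, which is harder to summarise as a short list of risk factors. No data collection, sample size or treatment comparison changes.
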